### 2.3. Research Design and Sampling

This is a quasiexperimental study with a control group (parallel design) that will be performed on 114 primiparous women. Sampling will be done in three health centers. To complete the sampling in group A, the researcher will refer to Lolagar Health Center. Due to the presence of more husbands of nulliparous women in childbirth preparation classes, Azadi health center was allocated to complete the sampling process in group B, and finally Tehransar health center will be to complete the control group. Participants will be equally and not randomly divided into two study groups of A and B and one control group (Figure 1). Spouses of the participants in study groups A and B will be trained virtually and face-to-face, respectively. Also, the spouses in the control group will receive no education regarding childbirth preparation during pregnancy.

Based on the study's objectives, a Telegram channel called: “Virtual childbirth preparation courses for fathers” will be created for uploading the educational content. The educational contents will be provided based on the standard regulations of Iran.

To increase the quality of training and prevent sending the whole content at once, the content of each session will be provided in sections that will be uploaded at a specific time. The educational contents will include five videocasts, four PDF files, and eight video files, which are shown in Table 1.

To ensure that the messages sent on the Telegram social media are read by the participants, before joining the group, they will be asked to share their last seen status with the researcher. Moreover, they will be required to become online at least once a day to watch the videos or read the messages. The last seen time of the participants will be controlled by the researcher, and those who are not online, do not see messages, or do not give feedback for seven days are initially contacted through message. In case of receiving no answer, the researcher will contact them through a phone call to ask for the reason. If needed, another cell phone number will be obtained to resend a message by Telegram social media to that number. Otherwise, the participant will be excluded from the study.

On the other hand, participants in the study group B will receive face-to-face training, and the content of the first and third sessions will be provided to the spouses in the form of an educational booklet. The contents of the second and fourth sessions will be based on the third and eighth sessions of childbirth preparation classes at the Azadi health center with the presence of spouses. The teaching will be performed in the form of a lecture by the midwife using teaching aids for 90 minutes. Educational content will be taught in accordance with men's educational needs to participate in childbirth preparation classes reviewed by Simbar et al. [15]. Table 1 presents the time, content, and objectives of the educational courses that are similar for both study groups. To increase the generalizability of the results, another group will be considered as the control group, the members of which will receive no educational courses about pregnancy and childbirth preparation whether through social media or face-to-face. It is important to note that all three groups will receive ordinary perinatal care. In addition, all participants will be followed up until 12 weeks after delivery.

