## 4. Discussion

This quasiexperimental clinical trial with the control group aims to compare the effect of virtual and face-to-face childbirth preparation training for spouses of the primiparous women on the pregnancy experience, FOC, and mother- and father-infant attachment. This study will be conducted by the Reproductive Health Department of the School of Nursing and Midwifery of Iran University of Medical Sciences, at the prenatal clinics of Lolagar Hospital and Azadi and Tehransar health centers. The main results of this study will help to improve the experience of pregnancy, reduce the FOC in pregnant women, and enhance the mother- and father-infant attachment.

To our knowledge, there are no published studies on the effect of two different educational methods on primiparous husbands on pregnancy experience, fear of childbirth, and parental attachment to the infant. This proposed project examines an educational intervention whose content is based on a qualitative study that investigates the educational needs of men to participate in prenatal care [15]. E-learning can solve some of the problems that exist in our country in the field of childbirth preparation courses through its interactive, self-guiding, and flexible nature. It is hoped that in such educational intervention two different educational methods will produce more favorable health outcomes. The use of new educational methods such as mobile software shows more desire of participants to participate in training classes. As a result, the strengths of this study will be the key to potential success. If e-learning can have the same effect on the outcomes of this study as face-to-face training, this method can be a useful way to increase the participation in childbirth preparation classes for those men who cannot attend childbirth preparation classes in person. If successful, the intervention may be adopted in other populations with other outcome and randomized clinical trial study designs. By using new educational systems such as e-learning, we can overcome educational problems such as lack of time and special place for education, and the need for experienced and trained people for education. Also, a range of outcomes relating to men's involvement in childbirth preparation courses will be assessed.

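### Follow-up to secure engagement is described only for the virtual group, and nothing comparable for the face-to-face group's two booklet sessions, so virtual versus face-to-face is not a comparison of teaching mode alone

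*Protocol article*

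**What the plan says.** All references are to the protocol article.

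**Group A (virtual), Section 2.3.** Before joining, the men agree that "they will be asked to share their last seen status with the researcher", and they must be online at least once a day. "The last seen time of the participants will be controlled by the researcher". After a week of inactivity the routine starts: "those who are not online, do not see messages, or do not give feedback for seven days are initially contacted through message". If there is no answer, "the researcher will contact them through a phone call to ask for the reason", and the message may be resent to another number. The last step is "Otherwise, the participant will be excluded from the study". Section 2.2 separately excludes group A men who send no feedback at all.

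**Group B (face-to-face), Section 2.3.** Half of the course is not taught in person: "the content of the first and third sessions will be provided to the spouses in the form of an educational booklet". The other half is taught in 90-minute lectures with the husbands present: "The contents of the second and fourth sessions will be based on the third and eighth sessions of childbirth preparation classes". Section 2.2 excludes group B men on the basis of attendance. No reading check, feedback request, message or call is described for the booklet.

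**Use of the comparison.** Virtual versus face-to-face is the stated aim (Sections 1 and 4). Section 2.5 uses it for the difference that fixes the sample size. Section 2.3 calls the timing, content and objectives of the two courses similar. Section 4 draws a practical conclusion for men who cannot attend in person: "If e-learning can have the same effect on the outcomes of this study as face-to-face training", virtual training would be a useful route for them.

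**The concern.** The two trained groups are presented as receiving similar content in two modes. As described, they also differ in how hard the study works to make sure the content is taken in, and in who is removed for not taking it in. These are two separate problems:

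- **Support.** If prompting raises uptake in A, part of any advantage for A belongs to the prompting. If face-to-face teaching is in truth better but the booklets go largely unread, that advantage could be masked and the groups could look alike.
- **Selection.** Group A loses men who stay silent on Telegram; group B loses men who miss classes. The men who remain have passed different filters. Section 2.2 describes no filter on the husbands' engagement in the control group, so comparisons with control are affected too.

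At stake is the recommendation in Section 4. It treats similar results in A and B as evidence about e-learning, when uptake of half of B's course is not described as being recorded.

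**Working it through.** **Step 1: the comparison affected is the one the trial is sized on.** Section 2.5 gives two values for fear of childbirth, 25.1 and 18.9 (printed as deltas, read here as standard deviations), a difference of 15 between the face-to-face and virtual groups, alpha 0.05 and beta 0.2. Sidedness is not stated.

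- n per group = (1.96 + 0.84)² × (25.1² + 18.9²) / 15² = 7.85 × 987.22 / 225 = 34.4, so 35. This matches the plan's 35. A one-sided test would give 28, so a two-sided test was evidently used.
- Allowing for 10% dropout: 35 / 0.9 = 38.9, or 35 × 1.1 = 38.5. The plan recruits 38 per group, 114 in all. The rounding is immaterial here.

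**Step 2: delivery and adherence, session by session** (topics from Table 1, procedures from Sections 2.2 and 2.3).

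| Session | Topic | A: delivery and follow-up | B: delivery | B: adherence procedure described |
|---|---|---|---|---|
| 1 | Diet | Telegram; activity and feedback checked, message, call, exclusion | Booklet | None |
| 2 | Mental health, preparing for parenthood | As above | 90-minute class | Attendance rule; no reminder |
| 3 | Planning and type of delivery, pain control | As above | Booklet | None |
| 4 | Neonatal care | As above | 90-minute class | Attendance rule; no reminder |

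Group A has one routine across all four sessions. In group B the only rule concerns attendance, and only sessions 2 and 4 are attended. Two of four sessions therefore have no stated adherence criterion in B. One of them is session 3, whose topic plausibly lies closest to fear of childbirth.

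**Step 3: the measures differ as well.** In A, uptake is judged from online activity, messages seen and feedback sent. In B it is judged from presence in a room. Neither gives a figure per session that can be set beside the other, so the article as written offers no way to show that the four sessions reached the two groups equally.

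**Step 4: can the bias be sized?** That would need the effect of reminders on uptake and the effect of uptake on the outcome. The article gives neither. The 15 points in Section 2.5 are an A-B difference, not an effect of training against no training, so they cannot be shared out over sessions. What can be given is the precision against which any bias would act. With 35 per group, the standard error of the A-B difference is √(987.22 / 35) = 5.3 points, and about 1.96 × 5.3 = 10.4 points are needed for p < 0.05.

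**The case against.** The strongest reply is that prompting absent users is an ordinary part of remote delivery, just as a midwife and a 90-minute class belong to face-to-face delivery. Comparing two such packages is legitimate. Adding Telegram quizzes and calls to group B would put a virtual component into it and blur the contrast under study. This stands in part, and it shapes the fix. But the article does not define the comparison as one of packages: it calls the courses similar and draws a conclusion about e-learning.

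A second reply is that each group is a single centre without random allocation, so equalising follow-up would not free the comparison from confounding. That is true, and it makes this point secondary. Section 4 says random allocation is not possible. Unequal adherence procedures can be changed, and they are not among the limitations listed there.

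Several stronger readings are tempting, and the document does not support them:

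- A reader might infer that group B is not monitored at all. Attendance must be recorded for the exclusion rule to be applied.
- A reader might infer that group A men are pursued until they engage. The sequence is bounded and ends in exclusion, which brings in selection.
- A reader might infer that A's check shows only that the application was opened. Its triggers also include unseen messages and missing feedback.
- A reader might infer that no booklet check exists. A condensed article can show only that none is described.
- A reader might infer that a null result simply reflects unread booklets. If the modes were equally effective, unread booklets would favour A. Masking requires face-to-face teaching to be the better mode.

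**Conclusion.** The concern holds in this form: follow-up to secure engagement is described for group A only, nothing comparable is described for two of group B's four sessions, and the engagement exclusions differ between groups. Virtual versus face-to-face therefore mixes teaching mode with adherence support and with selection. Neither a difference nor its absence can be credited to mode alone.

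No size can be put on this from the document, and even its direction depends on whether prompting raises uptake and on which mode is truly better. Any figure in points on the fear scale would rest on invented inputs. The conclusion assumes that the silence about the booklet sessions reflects the actual procedure. If the full protocol describes an equivalent check, the support part falls away, but the different exclusion rules remain. The point ranks below the one-centre-per-group confounding, but it is cheap to correct and bears directly on the conclusion in Section 4.

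**What to change.** 1. **Record uptake in the same way.** For each of the four sessions, collect the same brief measure from every husband in A and B. In B this can be done on paper at the taught classes (booklet 1 at the session 2 class, booklet 3 at the session 4 class) or with the existing questionnaires at 37-38 weeks, so that no Telegram coaching is added.
2. **Report it.** Show uptake by session and group beside the A-B estimate.
3. **Describe, do not exclude.** Drop the group-specific engagement exclusions in Sections 2.2 and 2.3 and keep enrolled couples in the analysis whatever their engagement. The pregnancy experience and fear of childbirth scores come from the woman, so a husband's silence or absence need not prevent their collection.
4. **Settle what A versus B means.** Either apply a matching reminder rule to the booklet sessions, or state that the comparison is between delivery packages including follow-up. In the second case, limit the e-learning conclusion in Section 4 to virtual delivery with active follow-up, and add the unequal follow-up to the limitations.

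The cost is a short amendment and slightly more data collection in group B, about 38 husbands. Asking about a session may itself prompt some men to read or watch it; with the same questions in both groups this should be small and roughly balanced. Centre confounding is unchanged by any of this.

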**Methods:**

The primiparous women attending the prenatal clinics of Lolagar Hospital and Azadi and Tehransar health centers of Tehran along with their husbands will be studied. The inclusion criteria for the women's husbands are the first experience of becoming a father, being at least 18 years of age, and the ability to read and write. The exclusion criteria for women's husbands are the history of physical/mental illness; being a smoker; and consuming alcohol, drugs, or psychotropic substances. The participants will be selected by the convenience sampling method and will be divided into three groups of study A, study B, and control. Spouses in study groups A and B will receive childbirth training through virtual and face-to-face methods with similar content, respectively. The control group only receives ordinary prenatal care. At the 18–20 weeks of gestation, demographic information, pregnancy experience scale (PES), and version A of Wijma delivery expectancy/experience questionnaire (WDEQ-A) will be completed. At 37-38 weeks of gestation, the PES and WDEQ-A questionnaires will be completed again and maternal postnatal attachment scale (MPAS) and postnatal paternal-infant attachment questionnaire (PPAQ) will be completed by the parents 12 weeks after the delivery. *Discussion*. Improving the experience of pregnancy, especially reducing the FOC and creating a positive attitude towards it, is a vital strategy to promote vaginal childbirth and reduce the number of cesarean sections requested by women. Achieving this will reduce the cost of health care and improve the quality of life during pregnancy, after childbirth, and during the growth and development of infants. *Ethics and Dissemination*. This research has been funded by the Iran University of Medical Sciences, approved by the Thailand Registry of Clinical Trials, and will commence in May 2020. Results will be disseminated through peer-reviewed journals and shared with the academic and medical community to pregnancy and childbirth outcomes. This trial is registered with TCTR20200515011.

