## Figures and Tables

**Figure 1 fig1:**
[figure not shown]
Key points for data collection.

**Table 1 tab1:** The educational content of social media-based training group and face-to-face childbirth preparation courses group.

Time	Content	Objectives	Uploading the virtual content to the Telegram channel
First session: 24–28 gestational week	(1) Pregnancy diet	(1) Pregnancy diet with emphasis on what to eat (2) An introduction to the food pyramid	1 videocast and 2 video files for theoretical content
Second session: 28–30 gestational week	(1) Mental health during pregnancy	(1) An introduction to the fetal growth and development (2) Preparing for motherhood (3) Preparing for fatherhood	2 videocasts, 1 PDF, and 2 video files for theoretical content
Third session: 32-33 gestational week	(1) Planning for delivery and selecting the type of delivery	(1) Natural delivery vs. cesarean section (2) Different pain control methods during labor (3) Selecting the delivery location and necessary equipment for delivery	2 videocasts , 1 PDF, and 2 video files for theoretical content
Fourth session: 37 gestational week	(1) Neonatal care	(1) Neonatal care and risk factors	2 PDF files and 2 videos file for theoretical content

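### Group B is called face-to-face, but half its sessions, including the only one on labour and delivery, reach husbands as a booklet, so the A versus B contrast does not isolate delivery mode

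*Protocol article*

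**What the plan says.** The label is consistent across the article. The Abstract (Methods) says that the spouses in groups A and B "will receive childbirth training through virtual and face-to-face methods with similar content, respectively". Section 2.3 says: "Spouses of the participants in study groups A and B will be trained virtually and face-to-face, respectively". The Abstract (Background), the end of the Introduction and the Discussion all give the aim as comparing virtual with face-to-face training. Section 2.5 takes the fear-of-childbirth difference between the face-to-face and virtual groups as the basis for the sample size.

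The delivery of group B is set out further on in section 2.3. There, "the content of the first and third sessions will be provided to the spouses in the form of an educational booklet". For the other two sessions, "The contents of the second and fourth sessions will be based on the third and eighth sessions of childbirth preparation classes at the Azadi health" centre, with the husbands present; and "The teaching will be performed in the form of a lecture by the midwife using teaching aids for 90 minutes".

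Table 1 lists the content by session. Session 3 is headed "1) Planning for delivery and selecting the type of delivery", and its objectives include "2) Different pain control methods during labor". The table's delivery column describes the Telegram uploads only.

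The Discussion looks ahead to the reading of the A versus B result: "If e-learning can have the same effect on the outcomes of this study as face-to-face training", then the virtual method is offered as a useful route for men who cannot attend in person.

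**The concern.** An arm that carries one mode's name but is delivered half in another mode cannot answer a question about that mode alone. Here the half given in print includes the only session about labour and delivery, and fear of childbirth is the outcome that sizes the trial.

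What is at stake is the reading of the A versus B result. If the groups come out alike, the Discussion sentence invites the conclusion that e-learning can stand in for attendance. If they differ, the difference would be reported as one between virtual and face-to-face training. In either case the report would describe a group B that the trial did not deliver.

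**Working it through.** **1. The sample size rests on the A versus B contrast.** Inputs from section 2.5: SDs 25.1 and 18.9, difference 15, alpha 0.05 (taken as two-sided), power 80%, dropout 10%.

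- Common SD = √((25.1² + 18.9²)/2) = 22.22
- n per group = 2 × (22.22 × (1.960 + 0.842)/15)² = 34.44, rounded up to 35, as stated
- With dropout: 34.44/0.9 = 38.3, 35 × 1.1 = 38.5, or 35/0.9 = 38.9. The stated 38 agrees within rounding.

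The arithmetic is sound. The contrast that it describes is the one in question.

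**2. Mode by session, from section 2.3 and Table 1.**

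| Session (gestational week) | Topic | Group A (Telegram) | Group B |
|---|---|---|---|
| 1 (24–28) | Diet | 1 videocast, 2 videos | Booklet |
| 2 (28–30) | Mental health; fetal growth; preparing for parenthood | 2 videocasts, 1 PDF, 2 videos | Lecture |
| 3 (32–33) | Type of delivery, labour pain control, place of delivery | 2 videocasts, 1 PDF, 2 videos | Booklet |
| 4 (37) | Neonatal care | 2 PDFs, 2 videos | Lecture |

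The Telegram totals are 1 + 2 + 2 + 0 = 5 videocasts, 0 + 1 + 1 + 2 = 4 PDFs and 2 + 2 + 2 + 2 = 8 videos, which match section 2.3.

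**3. Counts for group B.**

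- Sessions in print: 2 of 4 (50%)
- Sessions on labour and delivery in print: 1 of 1, with all 3 of its listed objectives
- Sessions in person: 2 of 4. If the 90 minutes applies to each lecture, that is 2 × 90 = 180 minutes.

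**4. Timing.** Section 2.4 measures pregnancy experience and fear of childbirth at 37–38 weeks. Session 4 falls at week 37. Session 2, at 28–30 weeks, may therefore be the only in-person teaching that husbands receive well before those two outcomes are taken.

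**5. What A versus B compares.** For sessions 2 and 4 it is Telegram material against a lecture. For sessions 1 and 3 it is Telegram material against a booklet. The overall difference mixes the two, and the planned comparison cannot separate them. For delivery content there is no in-person component in either group of husbands.

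**The case against.** The strongest reply has five parts.

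- **Disclosure.** The booklet is stated openly, in the same sentence that introduces group B's face-to-face training. The similarity claimed between the programmes concerns time, content and objectives, not format. This is right: nothing is hidden, and the fault lies in the label and the inference.
- **Mode does vary.** A reader might infer that the trial does not test delivery mode at all. That goes too far. Sessions 2 and 4 do differ as virtual versus in person, and session 2, headed mental health during pregnancy, may plausibly bear on pregnancy experience and fear. Mode is not isolated, but it is not absent.
- **Hypotheses.** Section 1.2 states hypotheses against control only, and the Discussion sentence is conditional. A reader might infer a planned equivalence claim, or that the control comparisons fail too. Neither is supported. Each package can still be compared with control as far as this point goes. The aim and the sample size, however, do rest on A versus B.
- **Other explanations.** Each group comes from its own centre without randomisation (sections 2.1 and 2.3), so an A versus B difference could not be put down to booklet versus video either. That stands as a separate limit. Randomising would not cure this point, because group B would still be half print.
- **Exposure checks.** It is tempting to call session 3 monitored video against an unmonitored booklet. Group A's session 3 includes a PDF, and its checks (last-seen status, feedback) do not confirm viewing session by session. Group B has an attendance rule in section 2.2, though it cannot reach the booklet sessions. Follow-up of booklet reading is a detail that an article may leave to the full protocol.

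**Conclusion.** The point holds as one of arm definition and interpretation. Half of group B's sessions, and the only session on labour and delivery, are given to husbands in print. The A versus B result can speak to a Telegram package against a booklet-plus-two-lectures package. It cannot isolate virtual from face-to-face delivery, and a similar result would not show that e-learning matches in-person teaching, least of all about delivery.

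This rests on reading section 2.3 and Table 1 as written, with the session as the unit. The documents give no basis for saying how much the mixed delivery shifts the A versus B difference, or in which direction, so no size is put on that. The sample-size arithmetic and the comparisons with control in section 1.2 stand. The point should be corrected before the results are reported, but it does not invalidate the trial.

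**What to change.** - In the Abstract, the aim in the Introduction, sections 2.3 and 2.5, and the Discussion, describe group B as booklet (sessions 1 and 3) plus lectures (sessions 2 and 4).
- Add a group B delivery column to Table 1 beside the Telegram column.
- In the Discussion, limit A versus B conclusions to the two packages as delivered, and state that the fear-of-childbirth contrast is not evidence on face-to-face teaching of delivery content.
- Optionally, record the same short read-or-viewed confirmation for each session in both groups and report it by session.

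The cost is rewording, one table column and, if adopted, a one-line confirmation per session. The downside is a narrower claim than virtual versus face-to-face.
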